### **Measurement of blood pressure**

Special precautions will be taken to reduce the variation of BP value with resting BP. BP will be measured by 1) ensuring the participant rested for 10 minutes before the BP being measured, 2) using standard cuffs for adults fitted with a standard mercury sphygmomanometer, and 3) placing the stethoscope bell lightly over the pulsatile brachial artery on the right arm. Blood pressure will be recorded to the nearest 2 mmHg from the top of the mercury meniscus. Systolic pressure will be recorded at the first appearance of sounds, and diastolic pressure will be measured at phase V, that is, the disappearance of sounds. BP will be measured in both the sitting and standing position. Two readings will be taken 5 minutes apart, and the mean of the two will be taken as the final BP reading of the individual.

### **Foot examination**

The dorsalis pedis and posterior tibialis arteries will be palpated to identify peripheral vascular disease. Additionally, a 10-gram nylon monofilament and a 128 Hz tuning fork will be used to identify peripheral neuropathy.

### **Biochemical examination**

At first, an initial blood sample will be taken from the fingertip (70  $\mu$ L) by using a point of care machine to estimate the fasting plasma glucose (FPG), HbA1c, and fasting lipid profile. Then all the subjects will be given 75-gram oral glucose to drink and requested to wait for 2-hours for a second blood sample collection. During this 2-hour waiting time, they will be interviewed for the collection of socio-demographic information. Pre-formulated questionnaires will be used for this purpose. Each participant will be interviewed for approximately 25 to 30 minutes to complete the questionnaire. After completion of the interview, the anthropometric measurements and foot examination with monofilament, and tuning fork will be recorded. In addition, blood pressure will be recorded at this time. After 2 hours, a second blood sample for OGTT will be done by glucometer.

## The time frame of biochemical assessment

| Lab test              | Timing  |          |           |
|-----------------------|---------|----------|-----------|
|                       | 0 month | 4 months | 12 months |
| Fasting blood glucose | x       | x        | x         |
| 2h blood glucose      | X       | X        | X         |
| HbA 1c     | X       | X        | X         |
| Total cholesterol     | X       | X        | X         |
| Triglycerides         | X       | X        | X         |
| HDL-Cholesterol       | X       | X        | X         |
| LDL-Cholesterol       | X       | X        | X         |
| ECG                   | X       | X        | X         |
| Fundoscopy            | X       | X        | X         |

## Methods and specification of the machines for the various biological tests

| Test                     | Sample                | Method                | Specification of Machine                       |
|--------------------------|-----------------------|-----------------------|------------------------------------------------|
| OGTT
• FBG
• 2h AG | Capillary whole blood | Glucose dehydrogenase | Name of the analyzer
Alere G1 (South Korea) |
| T-Chol                   | Capillary whole blood | Enzymatic method      | Alere Cholestech LDX® (USA)                    |
| Tg                       | Do                    | Enzymatic method      | Do                                             |
| HDL                      | Do                    | Enzymatic method      | Do                                             |
| LDL                      | DO                    | Enzymatic method      | Do                                             |
| HbA 1c        | Capillary whole blood | Borrionate Affinity   | AFINION 2 (Norway)                             |

## Fundus Photography

We will collect retinal photographs using a non-mydratic digital fundus retinal camera and using a two-field imaging protocol (Canon CR6 non-mydratic retinal fundus camera). A retinal funduscopy machine will be used for taking retinal images. An Artificial Intelligence (AI) based algorithm will also be developed using retinal images to identify Diabetic Retinopathy (DR) cases.

## Definition of terms

- DM will be defined as if FPG  $\geq 7.0$  mmol/L or 2hPG  $\geq 11.1$  mmol/L. Prediabetes will be defined as FPG  $\geq 6.1$  mmol/L to  $< 7.0$  mmol/L (impaired fasting glycemia, IFG) and 2hPG  $\geq 7.8$  mmol/L to  $< 11.1$  mmol/L (impaired glucose tolerance, IGT). Normal glucose tolerance (NGT) will be defined as FPG  $< 6.1$  mmol/L and 2hPG  $< 7.8$  mmol/L. For screening of NGT, prediabetes, and DM, diagnostic criteria of WHO in 2006 will be used [33].

- Cut off points for general obesity for both sexes will be defined as BMI of  $\geq 25 \text{ kg/m}^2$  [35] and central obesity including WC for men and women will be  $\geq 90$  and  $\geq 80$  cm [34], and WHR for men  $\geq 0.90$  and women for  $\geq 0.80$  [36], respectively.
- Hypertension will be defined as systolic blood pressure (SBP) of 140 mm Hg or diastolic blood pressure (DBP) of 90 mm Hg or current treatment with antihypertensive medication [37].
- Cut-off values for serum lipid profiles will be high cholesterol (T-Chol)  $\geq 5.0 \text{ mmol/L}$ , high triglycerides (Tg)  $\geq 1.7 \text{ mmol/L}$ , high LDL-C  $\geq 3.4 \text{ mmol/L}$  and low HDL-C  $< 1.04 \text{ mmol/L}$  (for men) and  $< 1.3 \text{ mmol/L}$  (for women) [38].
- Dyslipidaemia will be defined as serum triglycerides  $\geq 1.70 \text{ mmol/L}$  for both sexes and HDL-C  $< 1.04 \text{ mmol/L}$  for men and  $< 1.3 \text{ mmol/L}$  for women [37].
- Bangladesh Diabetes Risk Score (BDRS) will be developed based on multiple logistic regression analysis using five simple parameters namely age ( $\leq 30 = 0$ ,  $31-40 = 3$ ,  $\geq 41 = 4$ ), sex (female = 0, male = 2), BMI ( $< 25 \text{ kg/m}^2 = 0$ ,  $\geq 25 \text{ kg/m}^2 = 2$ ), WHR (m  $< 0.90$ ; f  $< 0.80 = 0$ , m  $\geq 0.90$ ; f  $\geq 0.80 = 5$ ), and presence of HTN (no = 0, yes = 2). Subjects with a BDRS of  $< 5$  was categorized as low risk, 5 to 9 as medium risk and  $> 9$  as high risk for T2DM [32].
- Smoking habits will be classified as either current or non/ex-smoker.
- Socio-economic condition will be classified as low ( $< 5000$  Bangladeshi Taka [BDT, 1 USD = 84 BDT]), medium (5000-1000 BDT) and high ( $> 10000$  BDT) based on the monthly expenditure.
- Physical activity will be graded on a 1-3 ordinal scale based on leisure-time walking duration: light ( $< 30$  minutes), moderate (30-60 minutes), and heavy ( $> 60$  minutes). For data analysis, these categories will be transformed into a binary variable: inactive (grade 1:  $< 30$  minutes) and active (grades 2 and 3:  $\geq 30$  minutes) [39, 40].
- Diabetes-related knowledge will serve as a validated instrument assessing diabetes-related knowledge. There will be 11 questions, where correct answers will earn 1 point, while incorrect or “don’t know” responses will earn no points. This study will use a percentage score to evaluate knowledge [41].
- Health-Related Quality of Life of the participants will be assessed using the validated EuroQol-5D-5L scale and EuroQol-VAS score [42].

## 12. Data analysis

A data safety officer will monitor the study. The primary and secondary outcomes will be analysed using the intention-to-treat approach. Differences in baseline characteristics and clinical outcomes between the two groups will be evaluated using two-sample t-tests for continuous variables and chi-square tests for categorical variables.

For the primary outcome, the cumulative incidence of T2DM will be compared between the two groups using a log-rank test with random effects for intercept to account for pre-post correlations within participants. The intervention effect will be assessed at each time point. For secondary outcomes, which will be continuous variables, repeated-measure linear mixed models will be used to assess differences between groups over time.

The incidence rate of diabetes will be calculated by dividing the number of new diabetes cases by the total person-time of follow-up, expressed per 1,000 person-years. This method will account for participants with differing lengths of follow-up, including those who drop out or are lost to follow-up. Incidence rates will be

reported as events per 1,000 person-years, along with 95% confidence intervals (CIs), to provide a measure of precision and enable comparisons between groups.

The cumulative incidence of T2DM over the 12-month follow-up period will be estimated using Kaplan-Meier survival analysis. Differences between the survival curves will be tested using the log-rank test to determine statistical significance. To quantify the intervention effect, hazard ratios (HRs) with 95% CIs will be calculated using a Cox proportional hazards regression model, which will adjust for the time to diabetes development. Participants who do not develop T2DM or are lost to follow-up will be censored at the time of their last follow-up, ensuring accurate risk estimation.

For intervention measures, chi-square tests will be used to compare event rates between the intervention and control groups. Absolute risk reduction (ARR) and relative risk reduction (RRR) will be calculated, with risk ratios used to quantify the relative difference in event rates between the two groups. Confidence intervals for ARR and RRR will be computed to estimate the precision of the findings. The number needed to treat (NNT) to prevent one case of T2DM will be determined to evaluate the practical impact of the intervention.

Changes in biophysical, clinical, and laboratory parameters will be analyzed using a difference-in-differences approach, comparing changes within and between the intervention and control groups over time. This method will account for baseline differences and provide a robust estimate of the intervention effect. The difference-in-differences approach will be chosen because it isolates the intervention effect by controlling for time-invariant differences between groups and common trends over time. All analyses will be adjusted for clustering at the mosque level using mixed-effects models to account for intraclass correlation. Statistical significance will be set at  $p < 0.05$ , and all analyses will be performed using STATA version 17.0 (StataCorp, College Station, TX, USA) and the statistical package SPSS (PASW Statistics 20).

### **13. Health economic analysis**

Economic analyses (cost-efficacy/effectiveness and budget impact analyses) of those interventions implemented will be carried out under a limited societal perspective. Thus, direct (medical and non-medical), as well as indirect costs, will be considered. Direct medical costs will be collected alongside other clinical data generated in the trial. Direct non-medical and indirect costs will be collected by questionnaire.

We will focus on the impact of the intervention on economic outcomes including employment status, productivity loss (lost productivity due to ill health), expenditure, and assets (based on an asset index which will be computed from questions about ownership of assets, housing type and access to services). We will use two-stage models. First, we will evaluate the distributional impact of the intervention using difference-in-differences (DID) analysis to compare outcomes for the intervention group with the control group. In the second part, to evaluate the impact on economic outcomes, we will regress the predicted measure of T2DM morbidity from the first stage, on the economic outcome variables (e.g. productivity loss, catastrophic health spending). For each outcome, we will run appropriate regressions. We will take account of socio-demographic and other control variables including gender and will run sensitivity checks to ensure the robustness of our models.

### **14. Ethical approval:**

The study will be conducted according to the guidelines laid down in the Declaration of Helsinki. All procedures involved in this study will be approved by the Ethical Committee of the Diabetic Association of Bangladesh for Medical Research. Both witnessed and formally recorded verbal informed consent will be obtained from each subject along with written consent prior to inclusion in the study. This method was used to avoid selection bias due to the high literacy level of Bangladesh. Study participants will also be verbally informed of their right to

withdraw from the study at any stage or to omit their data from the analysis. Data collected for this study will be stored in a way that separated personal identifiers from all samples collected and the responses to all survey questions. Therefore, it will not be possible to identify respondents either directly or through identifiers linked to them. We will seek Clinical Trial Registration.

#### **15. Funding of the study/ budget:**

The total cost of the project will be met by the following sources:

- Non-Communicable Disease Control Program of Directorate General of Health Services, Ministry of Health and Family Welfare, Government of the People's Republic of Bangladesh

#### **16. Staff of the study:**

One (1) Principal Investigator, two (2) CO-PI, nine (9) Investigators, one (1) statistician, sixteen (16) Field Officers, twenty (20) Volunteers, one (1) Admin and Finance Officer, and one (1) Office Assistant will be recruited to conduct the study.

#### **17. Responsibilities of staff:**

**Principal investigator (PI):** PI, who will be employed for the whole period of study, will be responsible for the following:

- Overall coordination of the project
- Protocol development and ethical committee approval
- Liaising with funding agency
- Data clinging and analysis
- Report writing and dissemination

**Co-Investigator (Co-PI):** who will be employed for the whole period of study, will be responsible for the following:

- Coordination of project staff and investigators
- Protocol development and ethical committee approval
- Field visits
- Available 24 hours for assistance in case of any adverse events
- Data clinging and analysis

**Field Officers:** Sixteen (16) physicians working in different BADAS and its AAs will be employed for subject recruitment periods, and will be responsible for the following:

- Conducting structured interviews
- Clinical assessment
- Treatment if needed

**Volunteers:** The volunteers, who will be employed for subject recruitment periods, will be responsible for the following:

- First contact person who will discuss the study with the participants
- Obtaining informed consent
- Collection of anthropometric data
- Data entry

**Admin and finance officer:** The admin and finance officer will be employed for 8 months. He will be responsible for the following:

- Administrative and logistical activities
- Day to day finance and accounts related activities
- Financial reporting
- Supporting other staff

**Office assistant:** The finance assistant will be employed for 8 months.

- Messenger
- Photocopying documents
- Posting letters
- Storing papers, equipment

## 18. Governance and quality control

### 18.1 Data Monitoring and Ethics Committee (DMEC):

The **Data Monitoring and Ethics Committee (DMEC)**, comprising [name]. [name], [name], [name], and [name], will oversee the ethical conduct of the study and monitor data quality and safety. The DMEC will:

- Review study progress and ensure compliance with ethical guidelines.
- Monitor adverse events and ensure participant safety.
- Evaluate data quality and integrity throughout the study.

### 18.2 Trial Steering Committee (TSC):

The Trial Steering Committee (TSC), consisting of [name], [name] [name], [name], [name], and [name], will provide strategic oversight and guidance for the study. The TSC will:

- Review and approve the study protocol and any amendments.
- Monitor overall study progress and ensure alignment with research objectives.
- Provide expert advice on scientific, logistical, and ethical matters.

### Role of the Committees:

- **Ethical Oversight:** The DMEC will ensure that the study adheres to ethical standards and protects participant rights.
- **Data Integrity:** Both committees will monitor data collection and analysis to ensure accuracy and reliability.

- **Study Progress:** The TSC will provide guidance on study implementation and address any challenges that arise during the trial.

The study team will acknowledge the invaluable contributions of the Data Monitoring and Ethics Committee and the Trial Steering Committee for their guidance and support in ensuring the study's success. Their expertise and oversight will be critical in maintaining the study's ethical and scientific standards.

### **18.3. Data handling and record keeping:**

The following steps will be followed –

#### **18.3.1. Confidentiality:**

Information about study subjects will be kept confidential and managed according to the existing rules of the institutional review committee.

#### **18.3.2. Records retention:**

The correlation tool will be destroyed at the completion of the study in accordance with the health documentation destruction policy of the institutional review committee.

#### **18.3.3. Regulatory binder:**

A regulatory binder will be maintained for this study. This will include items such as this protocol, the letter of approval from the IRB, the Waiver of the Authorization form, and all other information pertinent to this study.

### **19. Reporting adverse events (AEs)**

Two investigators will be available 24 hours for assistance in case of any adverse events. Subjects will have 24 hours access to emergency inpatient services if related to the study. Records will be kept of any adverse effects occurring during the study and sent to the governance committees.

### **20. Indemnity**

The study will be indemnified by the Diabetic Association of Bangladesh.

### **21. Future perspectives**

Our findings will help to compile large hospital-based data and create an environment that will be conducive to promoting healthy lifestyles through multi-sectorial, inter-disciplinary collaborations.

### **22. Conflict of interest:**

No potential conflict of interest.

### **23. Report writing of the project:**

A report of the project will be delivered monthly by the investigator. A detailed report writing format will be developed based on the objectives of the study. Moreover, reports including financial reports will be submitted to BADAS and the funding agency at the end of the study.

### **24. Dissemination of the results:**

Scientific results will be published in international journals of diabetes or epidemiology. In addition, we will publish summary articles in the Journal of the Bangladesh Medical Association and the Medical Journal of BADAS. Further, results will be presented and discussed among the stakeholders in Bangladesh and at international conferences.

**25. Time frame:**

The duration of the study will be twelve months.

| Description/ Time in 1 months              | 1 | 2 | 3 | 4 | 5 | 6 | 7 | 8 | 9 | 10 | 11 | 12 |
|--------------------------------------------|---|---|---|---|---|---|---|---|---|----|----|----|
| Finalize the methodology, field assessment |   |   |   |   |   |   |   |   |   |    |    |    |
| Staff recruitment and training             |   |   |   |   |   |   |   |   |   |    |    |    |
| Development of data collection tool        |   |   |   |   |   |   |   |   |   |    |    |    |
| Ethical approval                           |   |   |   |   |   |   |   |   |   |    |    |    |
| Screening & patient enrollment             |   |   |   |   |   |   |   |   |   |    |    |    |
| Baseline information collection            |   |   |   |   |   |   |   |   |   |    |    |    |
| Intervention tool development              |   |   |   |   |   |   |   |   |   |    |    |    |
| Baseline assessment                        |   |   |   |   |   |   |   |   |   |    |    |    |
| Baseline data analysis                     |   |   |   |   |   |   |   |   |   |    |    |    |
| Intervention                               |   |   |   |   |   |   |   |   |   |    |    |    |
| End line Assessment                        |   |   |   |   |   |   |   |   |   |    |    |    |
| End line and total data analysis           |   |   |   |   |   |   |   |   |   |    |    |    |
| Report writing                             |   |   |   |   |   |   |   |   |   |    |    |    |
| Dissemination and validation               |   |   |   |   |   |   |   |   |   |    |    |    |
| Final Report Submission                    |   |   |   |   |   |   |   |   |   |    |    |    |

**26. Budget:**

| Cost Component                | Costs (BDT)  |
|-------------------------------|--------------|
| Staff Remuneration            | 1498720.00   |
| Laboratory Investigations     | 3,233,720.00 |
| Drafting and Printing         | 180,000.00   |
| Travel and Subsistence:       | 1,190,000.00 |
| Program Expenditure           | 2,998,000.00 |
| Equipments, Instruments etc.  | 160,000.00   |
| Use of Computer and Software  | 400,000.00   |
| Other Administrative Expenses | 302,400.00   |

|                    |                     |
|--------------------|---------------------|
| Grand Total | 9,962,840.00 |
|--------------------|---------------------|

## Statistical Analysis Plan (SAP)

**Study Title:** Faith-Based Lifestyle Intervention to Prevent Type 2 Diabetes Mellitus in Rural Bangladesh: A Cluster-Randomized Clinical Trial

**Trial Registration:** ISRCTN91564707

**SAP Version:** Retrospective Version 1.0 **Date:** 20 August 2023

**Declaration:** This SAP was developed retrospectively after completion of data collection and before analysis of primary outcomes. It reflects the prespecified analytical approach used in the manuscript. The SAP adheres to CONSORT 2010 guidelines for cluster-randomized trials.

### 1. Study Overview

This cluster-randomized controlled trial (cRCT) evaluated the effectiveness of a culturally tailored, mosque-based lifestyle intervention in preventing type 2 diabetes mellitus (T2DM) among adults with prediabetes in rural Bangladesh. Eight mosques were randomized (1:1) to intervention or control arms using a computer-generated block randomization schedule (block size = 2), stratified by district. Allocation was performed by an independent statistician; field staff enrolling participants were unaware of allocation until post-randomization. The study followed participants over 12 months.

**Intervention:** Monthly sermons by imams and trained female assistants (promoted healthy dietary practices, physical activity, and diabetes awareness. Control mosques received standard health education materials without structured sessions.

**Blinding:** Outcome assessors were blinded to allocation, but participants and intervention deliverers were not due to the behavioral nature of the trial.

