## 1. Abstract:

**Background:** Type 2 diabetes mellitus (T2DM) and related non-communicable diseases (NCDs) are significant public health challenges in Bangladesh, with a high prevalence among adults. Culturally tailored, faith-based interventions led by religious leaders have shown promise in promoting healthy behaviors and preventing T2DM. This study will evaluate the effectiveness of a faith-based lifestyle intervention delivered by mosque imams in reducing T2DM incidence and improving cardiometabolic outcomes among high-risk individuals in rural Bangladesh.

**Objectives:** The primary objective will be to assess the impact of a faith-based lifestyle intervention on the incidence of T2DM among high-risk individuals with prediabetes. Secondary objectives will include evaluating changes in cardiometabolic parameters, quality of life, and diabetes-related knowledge.

**Design:** A cluster-randomized controlled trial (RCT) will be conducted across eight mosques in rural Bangladesh. Mosques will be randomly assigned to either the intervention or control group. The intervention will consist of religious sermons promoting healthy behaviors, dietary guidance, and physical activity, while the control group will receive standard health education.

**Study areas:** The study will be conducted in eight mosques located in the districts of Manikganj, Narshingdi, Munshigonj, Dhaka, and Tangail. Four mosques will serve as intervention sites (Shibaloy, Monohardi, Raipura, and Dhanbari), and four will serve as control sites (Singair, Keraniganj, Sreenagar, and Sakhipur).

**Study duration:** 12 months (April 2022 to April 2023).

**Target population:** A total of 824 participants aged 25–65 years with prediabetes (based on WHO criteria) will be enrolled. Participants will be permanent residents of the study areas and willing to participate for the entire study duration.

**Statistical analysis:** The primary outcome will be the cumulative incidence of T2DM at 12 months. Secondary outcomes will include changes in weight, body mass index (BMI), blood pressure, blood glucose, lipid profiles, and quality of life. Data will be analyzed using intention-to-treat analysis, with comparisons between groups made using chi-square tests, t-tests, and mixed-effects models.

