## 10. Research methodology

### 10.1 Study design and participants

This cluster-randomized controlled trial (RCT) will be conducted across eight mosques in rural villages of five districts in Bangladesh: Manikganj, Narshingdi, Munshigonj, Dhaka, and Tangail. The study will target rural areas to address the unique challenges faced by these communities. Participants will be randomly allocated to either the intervention or control group at the cluster level (mosques). Eight mosques will be selected using a simple random procedure, with four assigned to the intervention group and four to the control group. Mosques will be randomly assigned as intervention or control sites using block randomization to ensure geographic diversity and balance across groups. Randomization lists will be generated centrally and concealed from field teams to minimize bias. Intervention centers will be in Shibaloy, Monohardi, Raipura, and Dhanbari, while control centers will be in Singair, Keraniganj, Sreenagar, and Sakhipur. All mosques are recognized by the Islamic Foundation of the Ministry of Religious Affairs and have an education center for learning the Holy Quran.

Participants will be recruited using the most recent voter list and age distribution data for Bangladesh. Each site will have an estimated population of 2,500 to 3,000 individuals, from which 1,500 individuals aged 25 to 65 years will be invited to participate. According to Bangladesh's age distribution, 45–47% of the population falls within this age group [30, 31]. The target recruitment goal is to enroll up to 108 participants from each mosque.

Recruitment will initiate at each mosque 4 weeks before the introduction of the intervention. The Imams will discuss and convey the message of a healthy lifestyle including diet and exercise during the Friday sermon and use a standardized script to encourage congregational participation in practice. They will distribute investigator-developed flyers to congregational participants to promote the study objectives. They will also discuss the importance of female participation as part of the intervention. Members of the research team will also attend Friday sermons to assist with recruitment and provide information regarding the study.

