### 10.7. Randomization and Masking

Participants will be randomized after the project research team determined that they:

1. Will demonstrate a satisfactory interest in joining lifestyle intervention during the run-in.
2. Will express willingness to continue in the trial.
3. Will meet all inclusion/exclusion criteria.
4. Will provide all baseline data.

After exclusions, 824 participants will be allocated at random in a 1:1 ratio to an intensive lifestyle intervention to promote increased physical activity and dietary modification or to minimal lifestyle advice to the control group. Randomization lists will be generated and supplied by the coordinating center, and staff who will perform the baseline measurements will have no access to the randomization lists. Neither staff delivering the intervention nor participants will be masked to the study arm.

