### 3. Trial Design and Randomization

A cluster-randomized parallel-group design was used with 8 mosques as units of randomization. Mosques were randomized 1:1 to intervention or control groups using a computer-generated block randomization schedule (block size = 2), stratified by district. The allocation sequence was prepared by an independent statistician. Field staff enrolled participants and assigned them post-randomization.

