**Analysis:**

- Kaplan-Meier survival curves estimated cumulative incidence.
- Group comparisons were assessed via log-rank test.
- Cox proportional hazards model with shared frailty for mosque-level clustering was used.
- HRs with 95% CIs were reported.
- The assumption of proportional hazards was tested using Schoenfeld residuals.

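### Concealment at enrolment is not demonstrated, the district blocks of two cannot all fill, and the primary analysis has no baseline glucose term

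*Combined protocol and SAP*

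**What the plan says.** **Unit and order of allocation**

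- Protocol 10.1 makes the mosque the unit and prints the result: "Intervention centers will be in Shibaloy, Monohardi, Raipura, and Dhanbari, while control centers will be in Singair, Keraniganj, Sreenagar, and Sakhipur". It also says the lists are kept from field teams, and that "Recruitment will initiate at each mosque 4 weeks before the introduction of the intervention". Imams promote the study in Friday sermons (10.1 and section 11, Phase 1).
- Protocol 10.7 words the step at participant level: "After exclusions, 824 participants will be allocated at random in a 1:1 ratio". It places this after eligibility, run-in and baseline data. One entry condition is "Will demonstrate a satisfactory interest in joining lifestyle intervention during the run-in". Staff taking baseline measurements have no access to the lists, but those delivering the intervention are not masked.
- The study timetable in protocol section 11 puts randomisation at the screening visit.
- SAP section 1 says that "field staff enrolling participants were unaware of allocation until post-randomization". SAP section 3 says field staff enrolled participants and made the assignment after randomisation.

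**Scheme**

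- SAP sections 1 and 3 give a "computer-generated block randomization schedule (block size = 2), stratified by district". Protocol 10.1 places the eight mosques in five districts.

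**Primary analysis**

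- SAP 7.2 lists Kaplan-Meier curves, a log-rank test and a Cox model: "Cox proportional hazards model with shared frailty for mosque-level clustering was used". No covariate is named there, and protocol section 12 names no baseline covariate for its Cox model.
- Adjustment for baseline values appears only in SAP 7.3, for secondary outcomes.

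**The concern.** When whole mosques are allocated, a person's arm is fixed by where he or she prays or lives. Anyone who knows a mosque's arm knows the arm of every candidate there, before risk scoring, consent and the glucose test. What matters for concealment is therefore whether enrolment at a mosque was finished before its arm was disclosed. Awareness at the moment of randomisation does not answer that.

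Several people involved in recruitment could have known. Imams promote the study, and in the intervention arm they deliver it and are paid for doing so. The volunteers who obtain consent (protocol section 17) are trained in delivering the intervention (section 11, Phase 2). Entry also depends on a judgement of interest. If arms were known, the people enrolled could differ between arms in their risk of progression.

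The primary endpoint is crossing a fasting or 2-hour glucose threshold, and the same two measures define entry. A difference in baseline glucose between arms would feed directly into the unadjusted hazard ratio. The mosque frailty describes correlation within mosques; it does not remove a systematic difference between arms.

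**Working it through.** **1. What the SAP sentence can mean.** There are two possible orders.

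- Mosques allocated first, participants enrolled later: staff can be unaware until randomisation and still know the arm at every consent. The sentence is true and gives no concealment at enrolment.
- Participants enrolled first, mosques allocated later: the sentence does imply concealment.

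Protocol 10.7 points to the second order. The printed arm list in 10.1, followed by a description of recruitment, points to the first. The timetable puts consent, eligibility, run-in and randomisation at one visit. SAP section 3 dates the assignment, not the enrolment. No date of allocation, disclosure or enrolment is given for any mosque.

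**2. Blocks of two within district.** Inputs: 8 mosques, 5 districts (protocol 10.1), at least one mosque in each. The possible splits are:

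| Mosques per district | Odd districts | Full blocks | Single-mosque districts |
|---|---|---|---|
| 2, 2, 2, 1, 1 | 2 | 3 | 2 |
| 3, 2, 1, 1, 1 | 4 | 2 | 3 |
| 4, 1, 1, 1, 1 | 4 | 2 | 4 |

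Full blocks balance themselves. Each odd district leaves one mosque in an unfilled block, which is in effect a fair coin toss. An exact 4:4 split needs the leftover mosques to divide evenly:

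- 2 odd districts: 2/4 = 1/2
- 4 odd districts: C(4,2)/2^4 = 6/16 = 0.375

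In every single-mosque district, arm and district cannot be separated.

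**3. Chance imbalance with four mosques per arm.** The plan's own design effect reproduces: 1 + (103 − 1) × 0.05 = 6.1. With the analysed sample (799/8, about 100 per mosque, 400 per arm) and the same ICC assumed for baseline glucose:

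- design effect = 1 + 99 × 0.05 = 5.95
- SE of the arm difference = sqrt(2 × 5.95/400) = 0.172 SD
- under individual randomisation = sqrt(2/400) = 0.071 SD
- 95% limits = ±1.96 × 0.172 = ±0.34 SD
- typical absolute imbalance = 0.172 × sqrt(2/π) = 0.14 SD

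With other ICC values the SE is 0.122 SD (ICC 0.02, limits ±0.24) or 0.156 SD (ICC 0.039, limits ±0.31). The documents give no ICC for baseline glucose.

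**4. Effect on the estimate.** Assume the odds of diabetes rise 1.5 to 2.5-fold per SD of baseline glucose; the documents give no figure. The same arithmetic applies if the multiplier is read as a hazard ratio.

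- typical imbalance (0.138 SD before rounding): 1.5^0.138 = 1.06 to 2.5^0.138 = 1.13
- 95% limit, 0.34 SD: 1.5^0.34 = 1.15 to 2.5^0.34 = 1.37

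**The case against.** The strongest reply is that the documents assert concealment more than once. Protocol 10.1 keeps the lists from field teams. Protocol 10.7 denies them to baseline staff and puts randomisation after baseline data. A reader might infer from the printed arm list that concealment failed, or that the SAP sentence is false. The text does not support that. The protocol mixes tenses (parts of 10.6, the run-in paragraph and section 14 are in the past), so the future tense does not date the list, and it may have been added after allocation. Nothing shows that any field worker knew an arm at consent. SAP section 3 attaches the timing to assignment, so enrolment before allocation is a natural reading.

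A reader might also take 10.7 as proof of individual randomisation. It may only be loose wording: 10.1 itself speaks of participants being allocated at cluster level, and mosques can be allocated after baseline.

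Differential selection is likewise not shown. The recruitment script is standardised, the interest criterion is not specific to an arm, and entry also requires a risk score and a glucose result.

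Finally, chance imbalance between few clusters is not bias. It would exist under perfect concealment, and the frailty term is meant to carry it into the interval, although eight mosques allow this only imperfectly.

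These replies limit the claim to lack of demonstration. They do not reconcile the timing statements, fill the blocks, or put a baseline term into the primary analysis.

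**Conclusion.** Three things stand on the text.

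1. The order of allocation, disclosure and enrolment is unreconciled, so concealment at enrolment is not demonstrated.
2. District-stratified blocks of two cannot all be filled with eight mosques in five districts. A 4:4 split was not guaranteed by the scheme (probability 1/2 or 3/8, assuming each leftover mosque is a fair toss), and arm is confounded with district in at least two districts.
3. The primary analysis has no baseline covariate, although the most obvious prognostic measures are scheduled at month 0 for everyone.

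A reader might take the 0.34 SD limit, or the 1.15 to 1.37 factor, as the size of a recruitment bias. It is neither an estimate nor a typical value. It is the outer limit of chance imbalance under an assumed ICC of 0.05 and an assumed risk gradient; the typical figure is 0.14 SD, a factor of 1.06 to 1.13. The documents report no actual baseline imbalance and give no basis for sizing recruitment bias. The concern is a risk that can be checked and partly addressed with data in hand.

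**What to change.** **Analysis.** Add to the primary outcome a Cox model with mosque frailty, adjusted for baseline fasting and 2-hour glucose, age and sex. Report it beside the unadjusted result. The SAP is dated after data collection and already reports an observed ICC, so list this model in SAP section 10 as added.

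The covariates should already be in the dataset: 10.7 requires complete baseline data, and both glucose measures are scheduled at month 0. The costs are a conditional rather than marginal hazard ratio and the post hoc label. Adjustment deals with measured baseline risk only; it would not remove selection on motivation.

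**Description.** Correct SAP sections 1 and 3 and protocol 10.7 so that they:

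- name the mosque as the only unit of randomisation;
- give each mosque's district and the strata and blocks actually used, including how unpaired mosques were allocated;
- give, per mosque, the dates of allocation, disclosure of the arm, and first and last enrolment, and bring the section 11 timetable into line.

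Where enrolment followed allocation, withdraw the concealment statement and report numbers screened, eligible and enrolled per mosque by arm. This costs wording and a table from the screening records. Recruitment itself can no longer be changed.
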